## Abstract

**ABSTRACT:**

**Introduction:**

Evidence suggests that sedentary behaviour (SB) and physical activity (PA) are important indicators of well-being and quality of life in older adults (OAs). However, OAs are the least active and highly sedentary of all the age groups. The present study intends to examine the feasibility of a wearable gadget to remind users to break sitting time (by standing up and moving more), coupled with a brief health coaching session, pamphlet and reminder messages to decrease SB and improve PA.

**Methods and analysis:**

This study will employ a multi-methods approach that generates quantitative data from questionnaires and qualitative data from semi-structured interviews following OAs’ involvement in the study. This intervention will be informed by the socio-ecological model (SEM) and the habit formation model. The quantitative and qualitative data will be analysed separately and then integrated for interpretation and reporting, which will assist our knowledge of the feasibility of the programme.

**Ethics and dissemination:**

Ethical approval for this study has been obtained from Swansea University (NM_ 2023 6667 6123). Informed consent will be obtained from participants. The findings of the study will be disseminated to the scientific community through conference presentations and scientific publications. The findings of the current study will determine the suitability of a future effectiveness trial.

**Trial registration number:**

NCT06407557.

STRENGTHS AND LIMITATIONS OF THIS STUDYThe current research will include multi-ethnic OAs (≥65 years) who are under-represented in research, allowing the findings to be generalised beyond the non-Black, Asian and Minority Ethnic OA population.Sedentary behaviour will be assessed via a self-reported (Measure of Older Adults’ Sedentary Time) tool rather than an objective measure, which limits the accurate assessment of sedentary behaviour.The design does not include a control group, thus not allowing outcome comparisons between groups of participants who have and have not received the intervention.It is difficult to draw conclusions on the long-term impacts of the intervention due to the lack of follow-up assessments incorporated to measure adherence to the intervention.

## Introduction

 The world’s population is rapidly ageing as life expectancy increases.^1 2^ The promotion of healthy ageing, that is, the process of developing and sustaining functional capacity that supports well-being in older age,^3^ means that older adults (OAs) are more likely to engage actively and contribute to cultural, social, economic and other important life domains.^4^ It is estimated that healthy ageing can lower the prevalence of non-communicable diseases^5^ and extend life expectancy by 0.68 years.^6^ Studies have shown that for healthy ageing, it is essential to complete an adequate level of physical activity (PA).^6 7^ PA has been defined as any skeletal muscle-driven movement of the body that involves energy expenditure.^8^ There is significant and consistent evidence that regular engagement in PA is linked with physical and mental health benefits.^9^ According to recommendations from the WHO, OAs (aged ≥60 years) should take part in 150–300 min per week of moderate-intensity aerobic activity or 75–150 min per week of vigorous-intensity aerobic activity, or an equivalent combination of moderate-intensity and vigorous-intensity aerobic activity. In addition, on 2 or more days per week, they should perform muscle-strengthening and balance activities (such as strength and resistance training and yoga) to maintain health and well-being.^8^ However, many OAs do not participate in PA at the intensity, duration or frequency needed to improve their physical and mental health.^10 11^

Evidence suggests that in addition to PA, sedentary behaviour (SB) is an essential indicator of well-being and quality of life in OAs.^12^ SB refers to any waking activity characterised by an energy expenditure of ≤1.5 metabolic equivalents, while in a sitting, reclining or lying position.^13^ OAs are identified as one of the most sedentary groups in the population, who spend 70.1% of their time being sedentary at home,^14^ and 67% of OAs spend more than 8.5 hours per day being sedentary.^15 16^ There is increasing evidence to suggest that SB is detrimental to physical health^17^ and is correlated with a higher risk of all-cause and cardiovascular disease mortality, type 2 diabetes^18^ and lower physical and functional quality of life.^19^ In addition, a high level of SB is negatively associated with cognitive function, functional status, depression and disability in OAs,^20^,^22^ impacting healthcare costs.^23 24^ Moreover, SB is related to a lower likelihood of successful ageing.^25^ Currently, there are no recommended guidelines that quantify a daily limit for sedentary time^16^; however, the Canadian 24-hour movement guidelines suggest that OAs should spend no more than 8 hours per day being sedentary.^26^ Hence to improve the quality of life in OAs, it is vital to minimise sedentary patterns and enhance activity.

Epidemiological and meta-analytic data show that both low levels of moderate to vigorous physical activity (MVPA) combined with substantial amounts of SB are simultaneously related to significant poor health outcomes and mortality.^27^,^29^ The WHO PA and SB 2020 recommendations encourage individuals to reduce extended sitting time; however, no particular technique has been suggested to help people reduce their sitting time.^30^ Presently, a few studies have assessed the feasibility of SB interventions that specifically target reducing OAs’ SB. The majority of these interventions have primarily focused on individual consultations and feedback sessions on behaviour change, action planning and goal setting.^31^,^36^ Additionally, a pilot study on OAs integrated a habit formation approach, aiming to replace SB with light activity. They used self-monitoring sheets every week and a booklet with techniques for overcoming extended periods of SB by introducing active habits to replace typically SBs.^37^ Findings from these intervention studies showed good feasibility and retention rates in minimising SB, highlighting that the interventions could successfully reduce SB.^37^ Hence, behaviour modification strategies have proved promising for minimising sitting behaviours and increasing activity.^38 39^ Furthermore, Rosenberg *et al*^40^ carried out an intervention study using wrist-worn wearable activity trackers (WATs; electronic wearable technologies used to track PA and SB) to provide vibrations after every 15 min to cue breaks to sedentary time during the entire day along with health coaching sessions and written materials. The study findings showed that the multi-component interventions could be implemented, as they demonstrated feasibility and increased OAs’ level of satisfaction with the intervention. However, these previous intervention studies have included younger adults with a minimal age of 50 years^33 41^ or 60 years,^3132 34^,^37 40^ although according to definitions and guidelines these people would not be classified as ‘older adults’ as they are not ≥65 years.^42^,^44^ Therefore, there has been limited research on the effectiveness of interventions to decrease SB, particularly among OAs.^45 46^ This is a significant omission since younger adults may benefit from different behaviour change techniques (BCTs) and interventions than those that may be of benefit for OAs.^47 48^ Including younger adults in these interventions might have positively influenced the results because younger people may be more willing to change their behaviour and face fewer barriers to breaking up their SB. Therefore, interventions that were successful in reducing SB in younger persons might not be feasible, acceptable or practical for OAs,^49 50^ resulting in the need to investigate the use of these interventions with OAs. Additionally, there is a dearth of studies including participants from the multi-ethnic sedentary OA group.^51 52^ Based on the high chronic disease prevalence in this group, research in this population is extremely important^53 54^ as they would arguably benefit more from SB reduction interventions than other ethnic groups of OAs.^32^,^37^ However, prior to conducting an intervention trial, it is important to assess the feasibility of an intervention, in accordance with the Medical Research Council (MRC) recommendations.^55^ In light of this, the current study aims to examine the feasibility of a multi-component intervention aimed at decreasing SB and employing a wearable device, along with a brief health coaching session, a pamphlet and reminder messages, with OAs who are at least 65 years old and come from a multi-ethnic background.

## Methods

### Study design overview

This study will employ a multi-methods design, generating quantitative data and using subsequent semi-structured interviews to produce qualitative data on OAs’ experiences of the intervention and procedures. This feasibility study will be carried out and reported in accordance with the Standard Protocol Items: Recommendations for Interventional Trial guidelines to ensure appropriateness of the reporting of the protocol^56^ (online supplemental file 1). The study will recruit approximately 20–25 OAs and is planned to be conducted between 1 January 2024 and 31 May 2024. This range of sample size is not based on statistical power but was an appropriate and practical sample for a feasibility study^57^ considering resource (time, money and effort) constraints. This sample size is similar to that used in other feasibility studies in previous studies of non-pharmacologic interventions that explored similar outcomes and led to further effectiveness trials.^31 36 49 50^

### Study intervention

The intervention will be based on behavioural theories,^58^ including the socio-ecological model^59^ and habit formation model.^60^ The socio-ecological model emphasises the importance of taking into account factors that may have an impact on SBs at the level of the built environment, including the home and outdoor environment. According to the principles of habit formation, automatic and unconscious processes have a particular influence on decisions to sit. Standing (rather than sitting) decision-making will become more automatic with practise if it is first brought into conscious awareness.

During the 12-week study period, OAs will receive an individualised face-to-face brief health coaching session lasting 40–60 min, along with a pamphlet, WAT and reminder messages via a mobile phone. In addition, the researcher will be available to the OA participants via telephone or email should they have any additional questions, problems or concerns throughout the study.

The neck-worn activity tracker provided to the OAs was built using off-the-shelf components, an Arduino MKR Zero microcontroller board (with SD card slot and Li-Po battery support), an Adafruit LIS3DH tri-axis accelerometer, an Adafruit PAM8302 mono 2.5W Class D audio amplifier, a thin plastic speaker (8 ohm, 0.25W), a vibrating mini motor disc, a 2000 mAh 3.7V Li-Po battery and a Raspberry Pi 4 enclosure and is unavailable for commercial use. It also has a power on/off button and a micro-USB cable for charging via the Arduino board. The device is worn around the neck using a lanyard or a similar cord. The accelerometer is used to detect the orientation and change of movement of the device along all three (X/Y/Z) axes. The device can detect activity through its movement and can detect whether the person is sedentary (sitting or lying down). Although thigh-worn accelerometers are more accurate compared with other accelerometers (hip-worn or wrist or neck),^61^ we did not consider thigh-worn accelerometers in the present research as our previous experience suggests there are significant cultural rules in this participant group around body exposure and modesty that would make this difficult. Wearing a thigh-worn device might be considered as exposing or intrusive, which could make the OAs in our study feel uncomfortable. In addition, certain religious customs include dress restrictions that emphasise covering certain body parts. Wearing a device on the thigh could contravene these dress regulations, which would discourage participants from using them. A review has also highlighted that the attitudes of minority ethnic participants towards PA were highly influenced by religion and cultural dress codes.^62 63^ Hence, wearing an electronic device affixed to their thigh may cause discomfort and be considered culturally inappropriate among ethnically diverse OAs. We therefore chose to use a neck-worn device for these reasons because it is more convenient for users to put on and take off and, in general, is also preferred by OAs.^64 65^ Given that OAs prefer easy and user-friendly technology,^66 67^ neck-worn trackers are simple to use because they have fewer features than other trackers^68^ and hence have prolonged battery life, which minimises the need for regular recharging—which some OA users may find intrusive. Nevertheless, given the evidence that wrist-worn devices are popular due to their convenience and comfort, this study will explore if future iterations of the device need to be modified to enable them to be worn on the wrist.^69^

The device aims to provide alerts through vibrations and voice-based sound messages (such as ‘Move More—Sit Less’; ‘Thrive for activity within home space’; ‘Hustle for that muscle within the home’; ‘The less I sit, the less stiff I get’; ‘Tune your body into fitness’ and ‘Keep calm and move within the home’) after every hour of being sedentary within the home that will act as a prompt/cue to prevent prolonged SB. Participants will be required to walk or stand for a few minutes at the time of the interruption from the alert. Via these breaks in SB, OAs will be asked to increase their daily steps throughout the day. The purpose is to counteract SB using target behaviours: replacing prolonged sitting with any amount of stepping or standing to break up the time spent being sedentary. The OAs will not be given any other feedback from the device which is standalone, and OAs will be asked to switch it off using the power switch when it is not needed, for example, during water-related activities or when they are out of the home socially. It is possible that the lanyard could get caught onto something during a fall, thus to mitigate against this, a cord that is easily broken or detached will be used. In addition, in the reminder messages, OAs will be encouraged to use the device. The researcher will be available to the OAs via message, telephone or email should they have any problems related to the device or any concerns throughout the study. The researcher will also use this as an opportunity to encourage participants to wear the device during the intervention period.

The information booklet produced by White *et al*^37^ detailing SB and PA information in relation to OAs’ health and well-being will be used to design the health coaching session and pamphlets. This will be reviewed by the research team who are experts in Sport and Exercise Science and have extensive experience working with OAs. The intervention material will be available in English. The brief health coaching session will enhance participants’ awareness of SB and PA, knowledge of the detrimental independent effects of SB and inactivity on the risk of chronic disease development, and provide examples of ways of reducing SB. Here, it will be important that participants become aware that interrupting sedentary time and enhancing activity is important throughout the day.

The intervention pamphlet will outline the term PA, its benefits and the recommended level. It will also explain SB and the difference between being active and being sedentary, discuss the Canadian 24-hour movement guidelines and highlight ways of using the home for enhancing activity and minimising SB. This includes an everyday cue (eg, ‘when TV ads…’) and a performance behaviour when encountering the cue (‘…stand up or start walking within your home’).^37^ These examples will include less or more intense variations of the suggested activities or behaviours within the home to enhance the likelihood of carrying them out.

The intervention pamphlet makes use of specific BCTs from the BCT taxonomy.^70 71^ The pamphlet promotes the benefits of activity and the health risks of prolonged sitting (ie, BCT 5.1: ‘Information about health consequences’’) and recommends lowering SB by directly substituting PA for existing sitting time (BCT 8.2: ‘Behaviour substitution’) or by enabling PA as one of the ways to replace sitting (BCT 4.1: ‘Instruction on how to perform behaviour’; BCT 13.2: ‘Framing/reframing’). The pamphlet explains that ‘PA’ not only refers to cardiovascular activity but also includes muscle-strengthening exercises, stretching and balancing. Additionally, it explains the habit formation technique and suggests including PA in daily routines, offering advice on how habits develop (BCT 8.3: ‘Habit formation’). Direction on forming habits is given through examples of activities that can be carried out within the home space, which will assist participants in minimising SB and increasing PA, improving their health and well-being. The pamphlet includes various examples of using the home environment to integrate activity into a daily routine (BCT 6.1: ‘Behaviour demonstration’) which, if practised regularly, will lead to a change in PA and SB habits (BCT 8.4: ‘Habit reversal’). These examples and reminder messages will act as cues to continue routine activity within the home environment (BCT 7.1: ‘Prompts/cues’) to reinforce and bring about favourable change in behaviour (BCT10.1: ‘Positive Reinforcement’). OAs will be asked to place the pamphlet in a convenient place that will remind them to use it frequently and make consulting it part of their daily behaviours.

The majority of behaviour modification programmes have transient benefits that dissipate when the intervention ends.^72^ This may indicate a gradual loss of motivation or external support.^73^ A sustainable intervention that reduces sedentary patterns and increases activity is therefore much needed. According to behavioural psychology, developing ‘habits’ can secure improvements in behaviour over time. Habitual behaviours are defined as activities motivated by impulses that are triggered by confronting a situation (environmental cue) in which the behaviour has been carried out on a regular basis in the past.^74^ Examples of environmental cues might be a person, location or prior activity within an established routine.^75^,^77^ A mental cue-behaviour association is strengthened by context-consistent repetition^78^ that triggers an impulse to perform necessary actions when an individual encounters a cue.^74^ Efforts and encouragement are needed to begin and maintain the early phases of the formation of habits; as the habit is formulated, control of behaviour is transferred to the external cue, and the activity requires less conscious effort to complete.^79^ As long as the cue is encountered, habitual behaviours are predicted to continue,^80 81^ possibly leading to self-perpetuating behaviour. Thus, habit development presents a viable strategy for sustaining the benefits of behavioural interventions following the termination of external support.^80^ The planned multi-component strategies will focus on how to alert oneself to have regular breaks from sitting which will help OAs use strategies to modify their inactive behaviour during the entire day.

### Eligibility criteria and recruitment

Different community organisations working with multi-ethnic OAs (eg, Asian community, African community) in Swansea will be contacted to request permission to recruit participants through their contacts and members. Local coordinators and sub-coordinators will be approached as they serve as gatekeepers to the recruitment of these OAs. Additionally, recruitment will be done via the sport, play and community networks of the city and county of Swansea, as well as advertising throughout the university where the researchers are located, using the intranet. Recruitment posters/leaflets, letters and email will be used for advertising the study.

Older individuals who are interested will be asked to contact the area project coordinator in their region to express their interest. The researcher will then contact interested participants. Those who are willing to participate will receive a study information sheet. The lead researcher will schedule a mutually agreeable time to meet with them and discuss the study process and procedures with them. If the OA is satisfied to proceed, they will be provided with a consent form to take part in the study.

We will employ a non-consecutive eligibility approach to recruit 20–25 participants from community organisations, which has been identified as a large enough sample to assess the feasibility of the intervention.^3157 82^,^85^ Eligible OAs aged ≥65 years, either male or female, sedentary (self-reported ≥5 total leisure hours sitting per day) and able to communicate in English or Urdu will be included. OAs with physical impairments that hinder them from participating in daily light-intensity PA, those who are currently engaged in daily MVPA (>150 minutes/week) or those who have participated in the past 3 months in a study promoting PA or reducing SB will be excluded. OAs with mental impairment, who are unable to provide informed consent or are unable to cooperate with the research team for the full duration of the project will not be included.

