### Feasibility assessment

The primary outcome is the acceptability and feasibility of the procedures of the intervention and recruitment and retention measurement. Recruitment rates were determined as the ratio of study participants who consented to participate out of those invited and eligible to participate. We will assess the attendance at, and time taken (minutes) for, the face-to-face health coaching session. Similarly, we will note the number of sent and successfully delivered messages and record the number of responses to, and acknowledgements of, the messages. Further, weekly reading/usage of the pamphlet will be recorded. We will use qualitative interviews to determine their overall user experience with the intervention which will help us to assess device feasibility by examining their perception regarding the vibrations and sound messages emitted from the device.

In addition, we will record drop-out reasons for discontinuing study participants, as well as adverse events experienced (eg, hospitalisation, life-threatening events, death). The suitability of measurement procedures will be evaluated based on the completion rates of the measures.

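### Eligible people are to be enrolled non-consecutively with no rule for who is offered a place, which may make recruitment, retention and acceptability look better by an unknown and invisible amount

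*Protocol article*

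**What the plan says.** Under Eligibility criteria and recruitment, the protocol article states the enrolment method: "We will employ a non-consecutive eligibility approach to recruit 20–25 participants from community organisations". The term is not defined further, and no reason is given for choosing it.

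The same section describes how people enter the study:

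- Advertising is open: "Recruitment posters/leaflets, letters and email will be used for advertising the study".
- Access to the community groups runs through intermediaries: "Local coordinators and sub-coordinators will be approached as they serve as gatekeepers to the recruitment of these OAs".
- Volunteers refer themselves: "Older individuals who are interested will be asked to contact the area project coordinator in their region to express their interest".
- Then: "The researcher will then contact interested participants". No order of contact is stated.
- Among the exclusions, people "unable to cooperate with the research team for the full duration of the project will not be included".

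Under Feasibility assessment: "The primary outcome is the acceptability and feasibility of the procedures of the intervention and recruitment and retention measurement". The recruitment rate is defined there: "Recruitment rates were determined as the ratio of study participants who consented to participate out of those invited and eligible to participate".

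The Abstract (Ethics and dissemination) says that the findings will determine the suitability of a future effectiveness trial. The Discussion says that including this group is important for generalising to it. The strengths and limitations box and the Discussion list self-reported sedentary time, no control group, no long-term follow-up and the researcher's dual role as limitations. Neither mentions selective enrolment.

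**The concern.** In most trials the order in which eligible people are taken matters little. Here recruitment, retention and acceptability are themselves what the study measures, so the rule for who is offered a place is part of the measurement. A non-consecutive method with no rule leaves that open.

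If there are more eligible volunteers than places, people who seem easier to schedule or more willing may be taken first. Consent, attendance, message response, completion and acceptability would then tend to rise together. The recruitment rate would not reveal this, because a person who is eligible but never invited is outside its denominator. There is no control group, so no internal comparison would reveal it either.

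At stake are the assumptions carried into the next trial: how many people must be approached, how much drop-out to allow for, and whether to proceed at all.

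**Working it through.** **Is there a figure to reproduce?** No. The only stated number is the sample of 20–25, which Study design overview says is not based on power. No target recruitment or retention rate is given. The check is therefore of mechanism and possible size, and every rate below is an assumption.

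**Step 1: does selection reach the outcome?** The enrolment method lets eligible people be passed over, and the recruitment rate is consented / (invited and eligible). A person passed over enters neither numerator nor denominator. Retention and acceptability are measured only on those enrolled. So any selection passes into all three, and none of them shows it.

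**Step 2: how large could it be?** Take two kinds of eligible person, keen (k) and less keen (l). Let s be the keen share of those invited, c the consent probability and r the retention probability.

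- Recruitment = s·c_k + (1 − s)·c_l
- Retention = [s·c_k·r_k + (1 − s)·c_l·r_l] / recruitment

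Compare s = 0.5 (invitations reflect an evenly mixed pool) with s = 0.9 (invitations favour the keen).

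| Assumed contrast | Recruitment, s = 0.5 → 0.9 | Retention, s = 0.5 → 0.9 |
|---|---|---|
| Strong: consent 0.90/0.30, retention 0.95/0.70 | 60% → 84% | 88.75% → 94.1% |
| Mild: consent 0.70/0.40, retention 0.90/0.80 | 55% → 67% | 86.4% → 89.4% |
| None: consent 0.60/0.60, retention 0.85/0.85 | 60% → 60% | 85% → 85% |

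For the strong contrast at s = 0.9, recruitment = 0.9 × 0.90 + 0.1 × 0.30 = 0.84, and retention = (0.9 × 0.90 × 0.95 + 0.1 × 0.30 × 0.70)/0.84 = 0.7905/0.84 = 0.941.

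The shifts are 24, 12 and 0 points on recruitment, and about 5, 3 and 0 points on retention.

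**Step 3: what must be true for a shift that large?** Reaching 25 participants at 84% consent takes 25/0.84, rounded up to 30 invitations, of which 0.9 × 30 = 27 go to keen people. If half the eligible pool is keen, the pool must hold at least 27/0.5 = 54 eligible people for 25 places. If everyone eligible is invited, s equals the pool's own share and the shift is zero.

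**Step 4: an extreme case.** Suppose 40 eligible people, half completing with probability 0.95 and half with 0.65, so average completion is 80%. If 22 places go to all 20 of the first kind and then to 2 of the second, completion is (20 × 0.95 + 2 × 0.65)/22 = 20.3/22 = 92%. That is 12 points higher, but it needs perfect sorting by motivation and an order of contact unrelated to motivation.

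**Step 5: scale of chance error.** An assumed 80% retention has an exact 95% interval of 56.3–94.3% at 16/20 and 59.3–93.2% at 20/25.

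**The case against.** The strongest reply is that no hand-picking is described. The study is advertised, interested people come forward, the researcher contacts them, and the willing are given information and a consent form. The eligibility text says that people meeting the criteria will be included. In a community sample with no sequential flow of patients, non-consecutive may mean no more than a volunteer sample. This stands. A reader might infer that the researcher or the coordinators will take the keenest volunteers, but the article does not say so. Nor does it say that the person who delivers the intervention and conducts the interviews also makes the recruitment contacts. The Discussion names only the first two roles, and discloses them.

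Second, selection needs surplus volunteers, and the article expects recruitment to be hard: Study timeline allows 3–4 months for 20–25 people, and the Discussion calls recruitment of this group a challenge. This also stands, and is why the range starts at nil.

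Third, most of the selection is self-referral, which consecutive enrolment does not remove. If keen people also respond first, order of contact gives the same 92% as the extreme case above. True. The fix removes only the discretionary layer, which is the part the investigators control.

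Fourth, the chance error is wider than any of these retention shifts. True, but an interval can be reported, whereas unlogged selection cannot be measured afterwards.

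Fifth, strict first-come enrolment could fill the places from whichever community answers fastest. This is a fair point against a single queue, and ordering within each community or route meets it.

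Finally, a journal article may leave the order of approach and screening logs to the full protocol. Their absence is therefore not held against the plan. The point rests on the method that the article does state.

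**Conclusion.** The point holds in a limited form. The article fixes an enrolment method that permits discretion over who is offered a place, in a study whose primary outcome includes recruitment, retention and acceptability. It also defines the recruitment rate so that such discretion would leave no trace.

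The likely direction is optimistic, on the assumption that discretion favours available and motivated people. The size is unknown and may be nil. The illustrations reach 24 points on recruitment and about 5 on retention under a strong assumed contrast and a pool of about twice the number of places. The 12-point retention shift is an extreme case and should not be taken as an estimate.

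A reader might go further and conclude that the results will not carry over to the next trial. The documents do not support that: a later trial using the same channels could draw similar volunteers. Separately, excluding people who cannot cooperate for the full duration also favours retention, whatever the enrolment order.

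**What to change.** 1. In Eligibility criteria and recruitment, replace the non-consecutive approach with offering places to eligible people in order of first contact, within each community or recruitment route so that the multi-ethnic mix is kept.
2. Keep a dated log, by route, of everyone who expressed interest, was eligible, was invited, was not invited (with the reason) and consented.
3. Report the recruitment rate as now defined and also out of all known eligible people. The second figure counts people who were never asked, so it shows how far selection went and is not a consent rate.
4. State volunteer self-selection as a remaining limitation beside the claim of generalisation.

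The cost is the dated contact log and slightly less freedom in scheduling. If few people come forward, ordering changes nothing, and the log will show that no one eligible was passed over.
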